### Study endpoints

The primary endpoint is the rate of unnecessary ICA occurring within 90 days in both groups as determined on a per patient level. Unnecessary ICA is defined as any ICA without haemodynamically significant CAD. The leading indicator for the evaluation of significant CAD is the functional measurement (FFR/iFR). If functional measurements are not available, then significant CAD is indicated by quantitative coronary angiography. Primary and secondary endpoints definitions are listed in Fig. S2 in Electronic Supplementary Material.

### Statistical analysis

#### Sample size calculation

We estimate that 28–41% of the patients who undergo ICA after CCTA do not have a haemodynamically significant stenosis [16, 17]. With the addition of FFRct we expect that the number of unnecessary ICA procedures will decrease by 33%. To reach an 80% power, a 0.05 significance level, and assuming a 10% drop-out rate, 528 patients need to be included in the trial (264 in each group).

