## Methods

### *Study design and population*

The FUSION trial is an investigator-initiated, multicentre, randomised, controlled trial in the Netherlands enrolling 528 patients with stable chest pain and 50–90% stenosis in at least one coronary artery ≥ 2 mm on CCTA. CCTA is performed for clinical indications, therefore CCTA itself is not part of the study procedures. The inclusion and exclusion criteria are presented in Tab. 2. Patients will be randomised on a 1:1 basis to receive FFRct-guided care or usual care, and will be followed up for a minimum of 1 year. Fig. 1 provides a flow chart illustrating the overview of the study design. The trial will start in 7 Dutch hospitals: Erasmus Medical Centre, University Medical Centre Groningen, University Medical Centre Utrecht, Adrz Hospital, Gelre Hospital, St. Jansdal Hospital, and Martini Hospital Groningen. Additional centres may join after the trial commences.

**Table 2 Tab2:** Inclusion and exclusion criteria

Inclusion criteria	Exclusion criteria
Age ≥ 18 years	Inability to provide informed consent
Stable chest pain	Unstable angina/acute coronary syndrome
Underwent CCTA with ≥ 50% but less than 90% stenosis in at least one major epicardial vessel with a diameter ≥ 2 mm	Unstable clinical status
	Expected inability to complete follow-up and comply with follow-up aspects of the protocol
	History of coronary revascularisation
	Non-invasive or invasive diagnostic testing for CAD within the past 12 months (with the exception of exercise ECG)
	Unsuitable for revascularisation if required (for example due to comorbidities or anatomical features)
	Poor CT quality with expected inability to perform FFRct analysis

*CAD* coronary artery disease, *CCTA* coronary computed tomography angiography, *ECG* electrocardiogram, *FFRct* computed tomography-derived fractional flow reserve

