#### The control group (usual care group)

All patients in the control group will undergo usual care. In case of an anatomical stenosis on CCTA, this often leads to ICA and invasive FFR measurement. The indication for ICA and revascularisation is at the discretion of the treating physician. It is recommended that the treating physician follows the European Society of Cardiology guidelines for the diagnosis and management of chronic coronary syndrome [2].

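### The sample size uses a rate among patients who undergo ICA, but the endpoint is counted per randomised patient, so the stated 80% power is supported only if usual-care ICA use and the unnecessary share are both high

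*Protocol article*

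**What the plan says.** The Protocol article, Sample size calculation, gives the planning rate as an estimate that 28–41% "of the patients who undergo ICA after CCTA do not have a haemodynamically significant stenosis". It expects FFRct to cut the number of unnecessary procedures by 33% and concludes: "To reach an 80% power, a 0.05 significance level, and assuming a 10% drop-out rate, 528 patients need to be included", that is, 264 per group. It names no single control rate and no proportion of usual-care patients expected to have ICA.

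Study endpoints defines the primary endpoint as the "rate of unnecessary ICA occurring within 90 days in both groups as determined on a per patient level". Data analysis specifies an intention-to-treat approach and a logistic regression of the outcome on random group assignment.

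The control-group section says of a stenosis on CCTA that "this often leads to ICA and invasive FFR measurement", and leaves the indication to the treating physician. The Discussion describes control-group care as resting mostly on ICA.

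**The concern.** The planning rate and the endpoint have different denominators. The rate describes patients who have already gone to ICA. The endpoint, read with intention to treat and a model on assignment, describes everyone randomised. The two are linked by

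control rate per randomised patient = P(ICA within 90 days in usual care) × P(unnecessary, given ICA).

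By the article's own description the first factor is below 1, so the control event rate is lower than the conditional share. At a fixed relative reduction, a lower control rate means less power. The conditional share is itself a range whose lower end needs far more patients than its middle.

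The Discussion says the result will feed a fast-track reimbursement assessment. A non-significant result would be read against a 20% chance of missing a true one-third reduction. If the real chance is higher, that reading would be wrong.

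**Working it through.** **Inputs from the article.** Conditional share 28–41% (midpoint 34.5%); relative reduction 33%; power 80%; significance level 0.05; drop-out 10%; 264 per group. **Assumed:** a two-sided test, and the usual-care ICA proportion, which is varied below.

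**Step 1: reproduce the plan.** Pooled two-proportion formula:

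n = [1.960·√(2p̄(1−p̄)) + 0.8416·√(p₁(1−p₁) + p₂(1−p₂))]² / (p₁−p₂)²

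With p₁ = 0.35, a one-third reduction to p₂ = 0.2333, and p̄ = 0.2917:

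n = (1.960 × 0.6428 + 0.8416 × 0.6375)² / 0.1167² = 237.1

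Dividing by 0.9 gives 263.4, so 264 per group. With exactly 33% instead of one third, the same control rate gives about 270 per group (540 in total). The plan's figure therefore corresponds to a control rate of about 35%, close to the midpoint of the conditional range.

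**Step 2: the ends of the stated range, with every control having ICA.** For a 33% reduction, 28% needs about 328 evaluable per group and 41% about 192. The plan has 264 × 0.9 = 237.6, taken as 238.

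**Step 3: power on the all-randomised denominator.** With p₁ = ICA proportion × share and p₂ = 0.67·p₁:

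power = Φ{[(p₁−p₂)√n − 1.960·√(2p̄(1−p̄))] / √(p₁(1−p₁) + p₂(1−p₂))}

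Example: share 28%, ICA proportion 100%, n = 238. Here p₁ = 0.28, p₂ = 0.1876, and (0.0924 × 15.43 − 1.960 × 0.5986) / 0.5950 = 0.42, so power is 66%.

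| Usual-care ICA proportion (assumed) | Share 28% | Share 34.5% | Share 41% |
|---|---|---|---|
| 100% | 66% | 78% | 88% |
| 90% | 60% | 72% | 82% |
| 80% | 54% | 66% | 76% |
| 70% | 48% | 58% | 68% |

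At 80% ICA use, a true 33% reduction would be missed in 24–46% of trials, against the stated 20%.

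**Step 4: where 80% is reached.** Setting power to 80% at n = 238 requires a control rate of about 35.4% per randomised patient. At a share of 41% that means ICA use of about 0.354/0.41 = 86%. At 34.5% or 28% it is not reached even with full ICA use. With no drop-out (264 per group) the required rate is about 32.9%, which is ICA use of 80% at a share of 41% and 95% at 34.5%.

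**Step 5: detectable reduction.** Solving the power formula for the relative reduction at 80% power and n = 238 gives 33% at a control rate of 35%, 38% at 28%, 41% at 25% and 44% at 22%.

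**The case against.** Four points can be made for the plan.

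- **The 35% may already include ICA use.** A reader might infer that 264 per group requires every control patient to have ICA. It does not: 41% × about 85% is also 35%. The article does not state the single rate, so it cannot show that the conversion was left out. This stands. What remains is that no conversion is stated, and that this route needs a share at the top of the cited range.
- **The shortfall is not fixed.** The words used for ICA in usual care put it below 100% but give no number. At a share of 41%, power is 82% with 90% ICA use. This stands, and it is why the result is a range.
- **The population may differ from the cited one.** Stenoses of 90% or more are excluded because they are very likely to be haemodynamically significant. If the cited populations included them, the unnecessary share here could exceed 28–41% and offset part of the loss. The sample-size paragraph does not invoke this.
- **The article is condensed.** The full endpoint definitions are in a supplementary figure that is not shown, so the all-randomised denominator is inferred from the per-patient wording, intention to treat and the model. Giving only a range is not in itself a fault of an article. The point here is a mismatch between two things the article does state. Counting only patients with ICA would not rescue the power, because fewer patients would be analysed. For a share of 34.5%, 237 per group before selection and equal ICA use in both groups, power is 74%, 69% and 63% at 90%, 80% and 70% ICA use. That comparison would also rest on a subset formed after randomisation, against intention to treat.

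**Conclusion.** The point holds in conditional form. The planning rate and the endpoint have different denominators, no conversion is given, and the flat 80% power is not supported unless usual-care ICA use and the unnecessary share are both high. At the lower end of the article's own range, power is 66% even if every control has ICA (71% with no drop-out). That figure needs no assumption about ICA use. Below full use, the loss depends on an ICA proportion the article does not give.

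A reader might go further and conclude that 528 patients cannot deliver 80% power. The article does not support that, because a share near 41% with ICA use of about 86% or more does deliver it.

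The results assume a two-sided 5% test, the normal approximation, a 33% relative reduction and 10% drop-out.

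**What to change.** Keep N at 528 and restate the sample-size paragraph:

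1. Give the control rate per randomised patient as the assumed usual-care ICA proportion within 90 days times the assumed unnecessary share, with one planning value for each.
2. Replace the flat 80% with the power at that rate, a table of power over plausible values of both factors, and the relative reduction detectable with 80% power.
3. If the exclusion of stenoses of 90% or more is expected to raise the unnecessary share, say so and include it in the planning value.

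Take the ICA proportion from external or pre-trial usual-care data. Pooled, allocation-blind ICA data from the trial are not a direct check. FFRct is meant to lower ICA use in one group, so the pooled proportion would fall below the control proportion if the intervention works as intended, and would overstate the shortfall.

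The cost is one rewritten paragraph and a stated power that is likely to be less favourable. No patients are added, and no endpoint or analysis changes.

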#### Data analysis

Statistical analysis will be performed using SPSS computer software and R software where necessary. Descriptive statistics will be used for presenting data. The analysis of the primary outcome and the secondary outcomes will use an intention-to-treat approach. A *p*-value of < 0.05 will be considered statistically significant.

In a logistic regression model we will analyse the association between the primary outcome and the random group assignment (FFRct versus usual care). The analysis will be performed both unadjusted and adjusted. Since we know from previous studies that age, sex, type of chest pain, and coronary artery calcium score are associated with haemodynamically significant CAD, we will adjust for these factors [18]. In a third model we will also analyse the effect of each participating centre with adjustment for the mentioned factors.

For the secondary endpoint, unnecessary ICA at 1 year and the other secondary endpoints similar statistical analyses will be performed as for the primary endpoint.

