## Background

In the Netherlands, 180,000 new patients present with stable chest pain—the most common symptom of coronary artery disease (CAD)—annually [1]. In the past few years, the preferred diagnostic strategy in these patients has evolved from a focus on functional testing to coronary computed tomography angiography (CCTA) [2, 3]. Treating cardiologists in the Netherlands are recommended to apply a more consistent management by using a single non-invasive first-line test for diagnosing CAD due to current variation in clinical practice [1]. Implementation of CCTA in the work-up of patients with stable chest pain, however, may lead to unnecessary invasive testing, because CCTA has the ability to accurately rule out CAD [4, 5], but not the ability to correctly predict a haemodynamically significant stenosis on invasive coronary angiography (ICA) [6].

Computed tomography-derived fractional flow reserve (FFRct) may overcome the shortcomings of CCTA. FFRct is a non-invasive method that uses the already acquired CCTA images as the basis to calculate coronary FFR values as they would be expected if measured invasively (see Fig. S1 in Electronic Supplementary material). FFRct applies computational fluid dynamics and deep-learning image-based modelling to estimate rest and hyperaemic coronary flow and pressure from CCTA [7]. FFRct represents the ratio of maximal coronary blood flow through a stenotic artery to the blood flow in the hypothetical case that the artery is normal [8]. Early validation studies, assessing the diagnostic performance of FFRct with invasive FFR as the reference standard, are promising. On a per vessel analysis, the sensitivity is 80–88% and the specificity is 61–86% [9–11].

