**Fig. 1 Fig1:**
[figure not shown]
Flow chart of the study design. * Clinicians are strongly discouraged from referring these patients for ICA. ** Patients are expected to be treated medically, but there may be instances whereby the clinician overrules this decision. *** Clinicians are encouraged to schedule ICA if coronary revascularisation is considered advisable. **** Decision for ICA depends on symptomatology, stenosis and FFRct location, extent of CAD, number of coronary arteries involved, and comorbidities. In some cases, one may first treat the patient medically to see if the complaints of chest pain disappear. *CAD* coronary artery disease, *CCTA* coronary computed tomography angiography, *FFRct* computed tomography-derived fractional flow reserve, *ICA* invasive coronary angiography

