### Study procedures

#### The intervention group (FFRct group)

In the intervention group, FFRct analysis will be performed based on the available CCTA data, without the need of additional imaging, radiation or medication. FFRct will be performed by HeartFlow, Inc. (Redwood City, California, United States) in all patients. A secure web transfer portal will be established with each site allowing transfer of the CCTA data to HeartFlow for FFRct analysis. The FFRct output will be returned to the investigating site within 1 working day [9]. Subsequently, the patient management strategy is determined with incorporation of the FFRct results (Fig. 1). In principle, patients with a negative FFRct (FFRct of > 0.80) should undergo conservative management. Patients with a positive FFRct (FFRct ≤ 0.80 for one or more focal stenoses in any coronary artery ≥ 2 mm) should undergo subsequent ICA.

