#### Post-hoc FFRct analysis in usual care group

Since in the intervention group, patients with FFRct > 0.80 will in principle not undergo ICA, false negative FFRct cases remain unidentified. Therefore, FFRct will also be performed in the usual care group (post-hoc FFRct), but will neither be revealed to the clinical site nor influence the diagnostic pathway. The treating clinician will be blinded to these FFRct results. This way, we can indirectly gauge the number of false negative FFRct findings retrospectively in patients who underwent ICA in the control group without influencing patient management in this group. A false negative is defined as negative FFRct result with an ICA showing haemodynamically significant stenosis on invasive FFR.

Data to be collected at baseline, 90 days and 1 year are presented in Electronic Supplementary Material.

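### FFRct status, available in both arms from the pre-randomisation CCTA, is in none of the three logistic models, so cheap precision goes unused; the gain is conditional and the planned analysis stays valid

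*Protocol article*

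**What the plan says.** The Data analysis section plans logistic regression of unnecessary ICA on randomised arm: unadjusted, adjusted, and in a third model that also examines centre. None is named as primary. The covariates come with a reason: "age, sex, type of chest pain, and coronary artery calcium score are associated with haemodynamically significant CAD, we will adjust for these factors". The approach is intention to treat.

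FFRct will be known for both arms. CCTA with a qualifying stenosis is an inclusion criterion (Table 2), so the scan precedes randomisation. In the FFRct arm, "FFRct analysis will be performed based on the available CCTA data, without the need of additional imaging". For controls, "FFRct will also be performed in the usual care group (post-hoc FFRct), but will neither be revealed to the clinical site". The control-arm values have two stated uses: gauging false negatives (post-hoc FFRct section, Discussion) and feeding the state-transition model (Cost-effectiveness analysis). The Discussion also plans to look at outcomes of FFRct-arm patients above 0.80.

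In the FFRct arm, a value above 0.80 points in principle to conservative management and a value of 0.80 or below to ICA, with room for judgement. The Fig. 1 legend says "Decision for ICA depends on symptomatology, stenosis and FFRct location, extent of CAD" and lists further factors.

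**The concern.** The primary endpoint is a joint event: an ICA is done and no haemodynamically significant CAD is found. The article selects covariates because they predict significant CAD. By that test FFRct is a strong candidate, since the Background credits it with 80–88% sensitivity and 61–86% specificity per vessel. The four listed factors may do less for this endpoint: whatever predicts CAD may also make ICA more likely, and the two effects can offset each other. The documents give no figure for this.

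FFRct is fixed by a scan that assignment cannot alter. What is randomised is whether the value is disclosed and used, so conditioning on the value does not bias the arm comparison. It is already being obtained in controls. Leaving it out of every model forgoes precision in a trial planned at 80% power, whose result feeds a reimbursement decision.

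**Working it through.** **1. The article's own figure.** The article states: "To reach an 80% power, a 0.05 significance level, and assuming a 10% drop-out rate, 528 patients need to be included". It gives a control range of 28–41% but no single planning rate. I assume 35%, a two-sided test and pooled variance:

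n = [1.96·√(2p̄(1−p̄)) + 0.842·√(p1(1−p1)+p2(1−p2))]² / (p1−p2)²

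With p1 = 0.35 falling by one third to 0.2333, n = 238 per arm. Then 238/0.9 rounds up to 265, so 530 in total. With a 33% fall (0.2345), n = 243 and the total is 540. Both lie close to 528, and no covariate enters.

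**2. Inputs for the comparison.** Control rate 0.345 (midpoint of 28–41%); intervention rate 0.345 × 0.67 = 0.2312; evaluable per arm 264 × 0.9 = 237.6. Assumed: per-vessel accuracy holds per patient; every control has ICA; FFRct-positive patients are handled alike in both arms.

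**3. Mid accuracy (sensitivity 84%, specificity 73.5%).**
- Share FFRct-negative: 0.345 × 0.735 + 0.655 × 0.16 = 0.358.
- Control risk of the endpoint: 0.2536/0.3584 = 0.708 if negative, 0.0914/0.6416 = 0.142 if positive.
- FFRct-arm risk: 0.142 if positive; (0.2312 − 0.0914)/0.3584 = 0.390 if negative. This means 0.390/0.708 = 55% of FFRct-negative patients still have ICA.
- Unadjusted variance sum: 0.345 × 0.655 + 0.2312 × 0.7688 = 0.404. The difference is 0.1139, its standard error √(0.404/237.6) = 0.0412, and power is 79%.
- Standardised by FFRct status: the within-stratum part is 0.316. The chance mix of strata combined with an effect that differs by stratum adds half the variance of that effect: 0.358 × 0.642 × 0.318² / 2 = 0.012. The sum is 0.328, the ratio 0.81 and power 86.5%.

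**4. Across the article's accuracy range.**

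| Sensitivity / specificity | Variance ratio | Power |
|---|---|---|
| 80% / 61% | 0.93 | 79% → 82% |
| 84% / 73.5% | 0.81 | 79% → 86.5% |
| 88% / 86% | 0.63 | 79% → 93% |

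Simulation of the mid case gave type I error of 4.9% unadjusted and 5.1% stratified.

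**5. Less ICA in usual care.** Hold the 33% reduction and send every FFRct-positive patient in the FFRct arm to ICA.

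| ICA in usual care | Power over the accuracy range |
|---|---|
| 85% | 69% → 71–83% |
| 80% | 66% → 67–78% |
| 60% | 51% → 51–57% |

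If FFRct-positive patients have ICA as often as controls do, the results are 66% → 68–79% at 80% and 51% → 52–59% at 60%. Across 60–80% the gain is thus about 0–13 points.

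**6. Where the gain disappears.** Let Δ be the risk in FFRct-negative minus FFRct-positive patients, and π the share negative. The variance saved is π(1−π)(Δ_control + Δ_FFRct)²/2. This is never negative in large samples, and it is zero when the two slopes cancel. Check at mid accuracy: 0.230 × (0.565 + 0.248)²/2 = 0.076, which is 0.404 − 0.328.

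Under good adherence Δ_FFRct turns negative. With assumed ICA rates of 10% in FFRct-negative and 100% in FFRct-positive patients of the FFRct arm, at mid accuracy, power moves from 94.9% to 95.6% (70% ICA in usual care) or from 76.7% to 78.0% (60%).

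**The case against.** The strongest reply is that nothing here is an error. A randomised comparison by intention to treat is valid with or without FFRct in the model, and 528 was set without adjustment. That stands. A reader might infer that the omission leaves the trial underpowered or biases the effect; the documents support neither.

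The size also depends on behaviour that the article does not expect. The mid case needs 55% of FFRct-negative patients in the FFRct arm to have ICA, although the article directs them in principle to conservative management, and it needs ICA in all controls, although usual care leaves ICA to the physician. This stands too, with one qualification. With full adherence the reduction is 1 − (1 − specificity)/(usual-care ICA rate), which is 51–82% at 80% ICA and 35–77% at 60%. The nil-gain setting therefore mostly goes with an effect larger than the planned 33%.

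Two further readings go too far. Using within-stratum variance alone gives a ratio of 0.78, 88% power and the equivalent of 28% more patients; with the term for varying effects it is 0.81, 86.5% and about 23% (0.404/0.328). And a reader might say that the plan hides where the effect arises. A comparison by FFRct status is commonly left to the analysis plan, which is not shown, so its absence from the article is no fault.

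The objection that covariate choice as a whole belongs in that plan does not stand: the article itself fixes the list and its reason.

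**Conclusion.** The point holds as a missed gain in efficiency. On the article's own criterion FFRct status belongs in the adjusted model, conditioning on it is legitimate, and the data are already planned. With ICA in all controls and the planned reduction, power rises from 79% to about 82–93%. With ICA in 60–80% of usual care the gain is about 0–13 points, and it is close to nil when FFRct-negative patients in the FFRct arm seldom have ICA. The figures rest on a 34.5% control rate, a two-sided test and per-vessel accuracy used per patient. They give no credit for what the four listed covariates already explain, which would shrink the gain. In none of these settings does the adjustment cost precision beyond simulation error.

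**What to change.** For unnecessary ICA at 90 days and at 1 year, add FFRct status to the adjusted model alongside the four listed factors, with levels above 0.80, 0.80 or below, and not analysable, and include an arm-by-status term. Standardise the arm effect to all randomised patients. This keeps intention to treat and gives one overall effect rather than an odds ratio conditional on FFRct. Apply the same reading process, and the same rule for calling a scan not analysable, in both arms. Report the arm difference within each FFRct stratum as supporting information.

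The cost is some wording and a few model terms, since the control-arm FFRct is already planned. The one real downside is timing: the adjusted analysis must wait until the control-arm FFRct results are complete and locked.
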